## Abstract

**Background:**

Poor adherence to antiretroviral treatment has been a public health challenge associated with the treatment of HIV. Although different adherence-supporting interventions have been reported, their long term feasibility in low income settings remains uncertain. Thus, there is a need to explore sustainable contextual adherence aids in such settings, and to test these using rigorous scientific designs. The current ubiquity of mobile phones in many resource-constrained settings, make it a contextually appropriate and relatively low cost means of supporting adherence. In India, mobile phones have wide usage and acceptability and are potentially feasible tools for enhancing adherence to medications. This paper presents the study protocol for a trial, to evaluate the influence of mobile phone reminders on adherence to first-line antiretroviral treatment in South India.

**Methods/Design:**

600 treatment naïve patients eligible for first-line treatment as per the national antiretroviral treatment guidelines will be recruited into the trial at two clinics in South India. Patients will be randomized into control and intervention arms. The control arm will receive the standard of care; the intervention arm will receive the standard of care plus mobile phone reminders. Each reminder will take the form of an automated call and a picture message. Reminders will be delivered once a week, at a time chosen by the patient. Patients will be followed up for 24 months or till the primary outcome i.e. virological failure, is reached, whichever is earlier. Self-reported adherence is a secondary outcome. Analysis is by intention-to-treat. A cost-effectiveness study of the intervention will also be carried out.

**Discussion:**

Stepping up telecommunications technology in resource-limited healthcare settings is a priority of the World Health Organization. The trial will evaluate if the use of mobile phone reminders can influence adherence to first-line antiretrovirals in an Indian context.

**Trial Registration:**

Trial registration: ISRCTN79261738.

## Background

In the current era of enhanced access to antiretroviral treatment (ART) globally, the number of people on ART in low and middle income countries by the end of 2008 has crossed the 4 million mark, with an increase of 1 million from the end of 2007[1]. However, one of the greatest challenges associated with the management of HIV is suboptimal adherence to antiretroviral therapy [2]. Good adherence to ART is beneficial to patients, as it minimizes treatment failure and prolongs survival. In addition, it has public health benefits. This is because poor adherence gives rise to the potential for development of drug-resistant strains [3], necessitating administration of expensive second-line therapy, and the possibility of transmission of drug-resistant HIV by non-adherent patients [4,5].

Adherence is known to be influenced by diverse characteristics of individuals, by their environments and by the treatment regimen prescribed [6]. There have been some successful interventions targeting patient-related social and psychological barriers to adherence, including Directly Administered ART (DAART) and peer support [7,8]. However, concerns have been raised over the quantum of healthcare resources that may be required to implement and sustain such expensive interventions, particularly in resource-constrained settings [6]. The Cochrane database of systematic reviews [9], reviewed studies of patient support and education for promoting adherence to ART. The 10-year review (1996-2005) included only studies, which used a randomized controlled trial design to assess the intervention and measured adherence at a minimum of 6 weeks. Only 19 studies met these inclusion criteria, and none of these had been conducted in low income settings (12 were in the US, 5 in Europe and 2 in Australia). Thus there is a need, particularly in low-income settings, to use sustainable contextual adherence aids, and to test these aids, using rigorous scientific design, at the population level.

There has been recent interest in the potential use of mobile phone technology for various aspects of health care, particularly in low-income settings [10-12]. Presently, 64% of all mobile phone users are in the developing world [13]. The current ubiquity of the mobile phone in resource-constrained settings [14], makes phone contacts a contextually appropriate, relatively low-cost means of supporting adherence. There have been few reports on the use of mobile phones in HIV care, within small cohorts of HIV patients from North [15]and South America [10], and Africa [16]. There have, so far, been no reports from randomized trials evaluating the influence of mobile phone reminders on adherence to ART; however a Kenyan trial evaluating this concept is currently ongoing [17].

India, which has over 275,000 patients on first line ART[18], is well suited to explore the influence of the mobile phone on adherence to ART, given the widespread connectivity, low costs and growing popularity of the mobile phone. Between 10 and 12 million connections are added every month to a base of 471 million connections [19]. Given that India is scaling up its national program for access to first-line ART, and that the use of the mobile phone is so widespread and relatively inexpensive, we plan to test in randomized controlled trial design, a hypothesis that mobile telephone reminders will influence adherence and hence time to virological failure in ART naïve, HIV infected patients, initiated on first-line therapy in South India. This protocol describes the methods proposed in the conduct of the trial.

## Methods/Design

This study is a two-centre, parallel group, randomized controlled trial. Eligible participants are randomized in a 1:1 allocation ratio to one of two arms: an intervention arm, in which the participants receive reminders via their mobile phones in addition to the standard of care(defined below); and a control arm in which they receive only the standard of care.

### Study setting and participants

Patients will be recruited from two institutions located in the capital cities of two different provinces in South India. One of these is an infectious disease clinic at a teaching university hospital in Bangalore, while the other is a comprehensive HIV treatment and care center in Chennai. Both are non-profit organizations with large clinics catering to both urban and rural populations in South India.

#### Inclusion criteria

Eligible participants include (i) HIV positive patients, (ii) between 18-60 years of age, (iii) who are ART naïve (defined as not having taken ART for more than 14 consecutive days previously),(iv) reside in the South Indian provinces, (v) and who meet criteria for initiation of first-line ART as per the national guidelines [20].

#### Exclusion criteria

Patients who are (i) severely ill (Karnofsky score[21] less than 70), (ii) those who are unable to participate in all study visits or (iii) those who reside in an area where there is no mobile telephone network will not be eligible to participate in the study. Further, to prevent contamination effects, patients belonging to a household where another member has already been recruited into the study, will not be eligible.

#### Informed consent

All eligible patients will individually be given an initial verbal description of the proposed study by a research assistant. Interested individuals will then be presented a written informed consent form. The form will also be verbally explained as there likely to be varying levels of literacy among potential participants. A signature, or thumb imprint, will be obtained from all those who consent to participate. The written informed consent form will be in English, Kannada and Tamil, as patients attending the study clinics speak one or more of these languages. Consent will be obtained by a trained research assistant, who is not involved in the routine clinical care of the patient.

### Randomization

Stratified randomization, separately for male and female participants, will be performed. Within each stratum, block randomization will be used to ensure balanced representation in the two treatment arms (control and intervention) as recruitment progresses. Blocks of 4 and 6 will be used. Sequentially numbered opaque sealed envelopes will serve as an allocation concealment method [22]. Envelopes will be located at the two study clinics. Once randomized, patients will be assigned to their respective study arms by a study nurse, and each will be given a study identification number.

### Intervention

The intervention which will be evaluated in this trial will consist of interactive voice and text messages sent to patients' mobile phones as reminders to take their ART. This intervention will be compared against the standard of care.

#### Standard of care

All patients in the study will receive the routine standard of care, as prescribed by the Indian national ART guidelines[18]. This will include three counseling sessions prior to initiation of ART, routine clinical and laboratory tests at baseline, and follow-up assessments as prescribed in the guidelines.

The intervention was designed following several discussions with the project team and with non-project clinical staff, as well as a pilot interview study with patients routinely attending the clinics [23].

The pilot study revealed that although 75% of patients owned mobile phones, use of the text messaging function was low, possibly because of relatively low literacy rates. Phones were used mostly for conversation. For the study intervention, an automated interactive voice message in the local language was selected, along with neutral pictorial messages instead of text messages, as these are language-independent and are less likely to lead to stigma should the phone be shared.

Thus the intervention will consist of 2 parts (i) an a *utomated voice call *that will go out once a week to patients in the intervention arm, at a time decided upon by each patient. The call will be interactive, as the patient will respond to a question about whether his or her pill doses were taken the previous day, by pressing '1' for yes or '2' for no. If the patient fails to respond to the call, a maximum of three more calls will be made over the ensuing 24 hours, until a response is obtained. (ii) A weekly non interactive neutral pictorial message will be sent out as a reminder 4 days after automated call.

All participants in the intervention arm will receive an explanation of the details of the intervention at recruitment. Participants will hear the recorded message that they will receive as an automated call, and informed of how to respond to this (clicking the digits 1 or 2 as appropriate). In addition, participants will also be trained on how to view messages on their phones and shown the image that they will receive as a reminder.

Patients in the control arm will also be given a mobile phone, but no interventions as described above will be made in this arm. This will be done to obviate any effect that simply 'receiving a mobile phone' might have on adherence.

Participants will receive the intervention at no added cost, as receiving calls or text messages are free within Indian phone networks. All participants (control and intervention) will be given air time credit of Rs. 100 (US$ 2.5) per month. Participants in both arms can call the clinic staff via their mobile phones whenever necessary, and a record of these calls will be maintained in a log book.

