### Ethical issues

The study protocol has been ethically approved by institutional ethical review boards in all the participating and collaborating institutions. The rights and welfare of the participants will be protected according to the Declaration of Helsinki Ethical Principles for Medical Research Involving Human Subjects. Clinical care and emergency medical services are provided by the participating institutions. Data that is collected as part of the study will be not be linked to any individual, personal identifiers will not be used in data storage, and confidentiality will be maintained at all levels of data management.

An important consideration in this study design is the possibility of stigma, as patients may not have disclosed their HIV status to people they live and work with. It is conceivable that some stigma may be attached to receiving a mobile phone from the hospital. Participants in the intervention arm also run the risk of being stigmatized, due to the receipt of regular text and voice messages. To minimize this risk, the picture messages that the patients will receive as reminders, will be neutral pictures, which the patient is shown, and approves at the enrollment visit. With regard to the automated call, the patient chooses a particular time based on his schedule, when s/he has the privacy to receive and respond to the call. Detailed counseling on potential stigma issues will accompany routine counseling at recruitment and at subsequent study visits.

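### The patient's chosen private time is the call-specific safeguard against disclosure, but the repeat-call rule is not tied to it

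*Protocol article*

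**What the plan says.** The procedure for the call is in the Protocol article under Intervention, in the text below the Standard of care subheading. The weekly automated call goes out "at a time decided upon by each patient". The patient answers by key press a question about "whether his or her pill doses were taken the previous day". The repeat rule is conditional: "If the patient fails to respond to the call", then "a maximum of three more calls will be made over the ensuing 24 hours, until a response is obtained". The picture is a second contact: "A weekly non interactive neutral pictorial message will be sent out as a reminder 4 days after automated call".

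The Ethical issues section gives the safeguards against stigma, and they differ by component. For the call the safeguard is timing: "the patient chooses a particular time based on his schedule, when s/he has the privacy to receive and respond to the call". For the picture it is content: the messages "will be neutral pictures, which the patient is shown, and approves at the enrollment visit". Counselling on stigma at recruitment and at later visits supports both.

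The Methods/Design part of the Abstract describes each reminder as a call together with a picture message, and says: "Reminders will be delivered once a week, at a time chosen by the patient".

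**The concern.** The safeguard for the call works only if the call arrives when the patient has privacy. The intervention text itself foresees that phones may be shared, and gives this as a reason for choosing neutral pictures. A spoken message in the local language does not have that protection, since whoever answers can understand it, so timing carries more weight for the call than for the picture.

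The repeat rule applies when the call at the chosen time has gone unanswered. One possible reason is that the patient was away from the phone or not alone. The rule then permits further calls over a whole day and says nothing to keep them within times the patient has accepted. At stake is a possible disclosure of HIV status, which is hard to undo. The question concerns participant privacy and not the comparison between the arms.

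**Working it through.** No sample size, power or event figure bears on this point, and the plan states no figure to reproduce. The check sets the sections side by side and makes one simple count.

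**Inputs**
- One scheduled call per week, at the patient's chosen time, written here as T (Intervention).
- Up to 3 repeats in the 24 hours after T, only if there is no response, ending once a response is obtained (Intervention).
- Call safeguard: a particular time with privacy, chosen by the patient (Ethical issues).
- Picture safeguard: neutral, patient-approved content (Ethical issues).
- Spacing of the repeats: not stated.

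**Count of calls**
1. Maximum call attempts in a week: 1 + 3 = 4.
2. In the window from just after T to T + 24 h, the chosen clock time occurs once, at T + 24 h.
3. If the repeats are made at different times, at most 1 of them can fall at the chosen clock time.
4. With all three made, the number outside the chosen time is at least 3 − 1 = 2 and at most 3. Of the four attempts, that is 2 to 3.
5. With two repeats made, at least 2 − 1 = 1 is outside. With one made, at least 1 − 1 = 0 is outside.

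As an illustration only, assume even spacing: 24 / 3 = 8 h, so the repeats come at T + 8, T + 16 and T + 24 h. The first two are outside the chosen time and the third coincides with it.

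**Safeguard against procedure, by contact**

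| Contact | Stated safeguard | Does the described procedure stay within it? |
|---|---|---|
| Scheduled weekly call | Chosen private time | Yes |
| Repeat calls after non-response | Chosen private time (the only call-specific measure) | Not tied to it; at least 2 of 3 outside if all are made at different times |
| Picture message, 4 days later | Neutral, approved content | Yes; timing is not its safeguard |

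**Abstract against procedure**
The Abstract presents the call and the picture as one weekly reminder at a chosen time. The intervention text describes two weekly contacts 4 days apart and attaches the chosen time only to the call. This is a mismatch in wording and does not show a breach of privacy.

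**The case against.** The strongest reply is that the Ethical issues section says the patient chooses a time for the call and does not promise that no call comes at any other time. The clock times of redials are operational detail that an article may leave to the full protocol or to the standard operating procedures, which the Quality Control section says exist. Silence on spacing does not show that the calls are unrestricted. This stands in part: the actual hours of the repeats are unknown, and the full procedures may already limit them. It does not remove the point. The article states a window of 24 hours for the repeats and names one call-specific safeguard, and that safeguard as worded does not cover the window.

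The existing mitigations also count. Repeats follow only non-response and stop once there is an answer. The text does not say that HIV is named. Patients have the intervention explained and hear the recorded message at recruitment, and stigma counselling continues at study visits.

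A reader might draw four stronger conclusions, which the documents do not support:
- **That the picture message also breaches the safeguard because it comes on another day.** Its protection is its content, and a 4-day gap says nothing about the hour of delivery.
- **That the repeat calls defeat protection against disclosure altogether.** The mitigations above rule that out.
- **That patients will be rung at work, among family or at night.** This is possible, but no redial hours are given.
- **That the planned comparison of telephone-reported with self-reported adherence is spoiled because someone else may press the key.** The procedure as described could not tell such a response apart, but nothing in the text shows that or how often it would happen.

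**Conclusion.** The point holds in limited form. The repeat-call rule weakens the stated call-timing safeguard but does not nullify it. When all three repeats are made at different times, at least two of the three fall outside the chosen time.

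The count treats the chosen time as a clock time. If the choice also fixes the day of the week, a repeat at T + 24 h is outside as well and the count becomes three of three. If it is meant as a longer private period, repeats made soon after the first call could fall inside it, although a rule worded over 24 hours does not confine them to that period. The article does not say which is meant.

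How many patients or weeks would be affected cannot be estimated, because the documents give no rate of unanswered calls. The matter is minor and has no bearing on the primary outcome, power or error rates.

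**What to change.** Reconcile the repeat-call rule in the Intervention section with the safeguard in Ethical issues, so that patient choice also covers repeat calls. One way, which extends the protocol's own principle, is to record at enrolment the times at which each patient accepts repeats and to set the automated system accordingly. If the operating procedures already do this, a sentence in the text saying so is enough. Separately, align the Abstract with the intervention text: two weekly contacts, a call and a picture message 4 days later, with a statement of which of them comes at the chosen time.

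The cost is one item on the enrolment form, one system setting and short edits to the text. The downside is slightly fewer answered repeat calls. The picture message needs no change on privacy grounds.

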### Outcome Measures

#### Primary outcome

The primary outcome will be measured as time (in weeks) to virological failure which defined as a plasma viral load of more than 400 copies/ml on each of two consecutive samples measured one month apart, six months after initiating ART. The date of the first assessment of a plasma viral load more than 400 copies/ml will be documented as the date of virological failure. Virological failure was chosen as a primary outcome, as this is a biological surrogate marker of poor adherence, and is an objective measure. For the primary outcome, patients in each arm will be followed up for 24 months (after initiating ART) or until virological failure occurs, whichever is earlier.

#### Secondary outcome

Participant adherence to ART during the study period of 24 months will be the secondary outcome. At each visit, adherence is measured using the 4-day recall [24] and the 30-day visual analogue scale [25]. A pill count is also done at every follow-up study visit.

### Quality Control

Standard operating procedures for key processes in the study have been developed. Prior to recruitment, the field team will receive extensive training on the objectives, methods and processes of the study, as well as on the concept of ethical research. In order to achieve optimal quality of data from questionnaires and laboratory tests, training and random checks by the site coordinator will be adopted. Completed questionnaires will be reviewed daily by the site coordinator for completeness, errors and inconsistencies. Quality assurance protocols will be set in place to maintain quality of processes and data collection in the clinic. In addition data collected will be subject to a second phase of checking through in built checks in the database (while entering data) and supervision of data entry by a trained person.

### Sample size

The primary end point in the trial will be time to virological failure as estimated using the standard life-table technique and illustrated by Kaplan Meier survival curves [26]. The baseline assumptions in the sample size calculation, are that the risk for virological failure in the control arm will be 10% [27] (risk rate 0.1), while the intervention will reduce this risk to 3% (0.03). The assumptions for this level of risk in the control arm and intervention arm are based on a review of available literature [8,28,29]. Stata 10 sample size software module was used to determine the necessary sample size for a comparison of the survival times between the two arms, using the log rank two-sided test. The significance level or alpha level was set to 0.05 for a two-tailed test, and the power (probability to detect a deviation of hazard ratio from unity) requested was 0.90 (90%). Given this, a sample size of 266 in each arm (n = 1:1) was determined. Assuming an attrition rate of 10%, this sample size was inflated by 10% to compensate for loss to follow-up, which gives a total sample of 292 in each arm. Thus a total of 600 patients newly initiated on ART will be recruited, with 300 in each arm of the trial. By having 300 participants in each arm, the trial will have sufficient power to detect a clinically significant difference between the arms. With a planned recruitment rate of 4-8 participants per week at each centre, the recruitments for the study will be completed within approximately 12 to18 months.

A flow diagram of the study design is presented in figure 1.

